### Diagnostic strategies

For a subject in high risk group according to each strategy, CCTA should be referred as the first-line CIT and other CIT, including noninvasive functional testing (NFT) and invasive coronary angiography (ICA), will be considered as an alternative. In both diagnostic strategies, subjects determined to be at low risk will be referred to optimal medication treatment (OMT) with no immediate CIT. The decisions regarding OMT will be done at discretion of the referring physicians according to recent primary prevention guidelines [24, 25], and is not a part of the study protocol. Thus, in cases where symptoms don’t resolve with maximum OMT, additional cardiac or non-cardiac diagnostic testing could be pursued as an escalation of the diagnostic strategy. Based on current SCP guidelines [3–5] and results of proposed researches [11–17], details of risk groups are illustrated in Fig. 1; Table 2 and as follows:

**Table 2 Tab2:** Low and high risk groups according to NICE and ESC strategy

	NICE strategy	ESC strategy
Low risk group	Both normal ECG and nonanginal chest pain	ESC-PTP ≤ 5%, or both 5%< ESC-PTP < 15% and RF-CL < 15%
High risk group	Typical and atypical angina, or nonanginal chest pain with abnormal ECG	ESC-PTP ≥ 15%, or both 5%< ESC-PTP < 15% and RF-CL ≥ 15%

ECG: electrocardiogram; NICE strategy: 2016 National Institute of Health and Care Excellence guideline-determined strategy; ESC strategy: 2019 European Society of Cardiology guideline-determined strategy; RF-CL: risk factor-weighted clinical likelihood; PTP: pretest probability

According to NICE strategy, subjects with nonanginal chest pain and normal ECG are classified into low risk group. Subjects with typical and atypical angina or nonanginal chest pain with abnormal ECG are classified into high risk group [5].

For each subject, ESC-PTP is calculated using age, sex and type of chest pain according to 2019 ESC guideline for the diagnosis and management of CCS [3] and RF-CL is calculated using age, sex, type of chest pain, hypertension, dyslipidemia, diabetes, smoking and family history of CAD based on the publication of Winther et al. [11], respectively. According to ESC strategy, subjects with ESC-PTP ≤ 5% are classified into low risk group and ones with ESC-PTP ≥ 15% are classified into high risk group [3]. For subjects with ESC-PTP of 5-15%, ones with RF-CL ≥ 15% are classified into high risk group and ones with RF-CL < 15% are classified into low risk group. The cut-off of 15% for RF-CL is chosen because RF-CL < 15% was associated with an extremely low prevalence of obstructive CAD and risk of clinical events [11, 16].

### CCTA and other CIT

All participating sites will use standard equipment, procedure and interpretation for CIT, as defined by current practice guidelines [3, 4, 26–29] and local protocols as previously described in the CICM-SCP registry [16, 22, 30]. All results will be reported by independent radiology/cardiology consultants with a minimum 5-year experience in the imaging modality and provided to the local physicians for subsequent decision making. The site interpretation of CIT was verified by central review of the clinical reports with review of the primary images as needed [31, 32]. The exercise electrocardiography criterion for a positive test was greater ≥ 1.5 mm of horizontal or down sloping ST segment deviation (depression or elevation) in any 2 leads except aVR for at least 60 to 80 ms after the end of the QRS complex, either during or after exercise. The criterion of single-photon emission computed tomography or positron emission tomography for a positive test was area of ischaemia ≥ 10% of the left ventricle myocardium. The stress echocardiography criterion for a positive test was ≥ 3 of 16 segments with stress-induced hypokinesia or akinesia. The criterion of cardiac magnetic resonance for a positive test was ≥ 2 of 16 segments with stress perfusion defects or ≥ 3 dobutamine-induced dysfunctional segments. The fractional flow reserve (FFR) derived from CCTA criterion for a positive test was FFR < 0.8.

Specially, CCTA images are acquired using 64-slice, or greater, multidetector CT scanners and all DICOM imaging data will be sent to the CCTA Core Laboratory (Tianjin Chest Hospital) for further analysis. In the CCTA Core Laboratory, all CCTA images will be analyzed by three experienced observers, 2 radiologists and 1 cardiologist, who are blinded to the other data. In image analyses, all segments ≥ 2 mm in diameter are identified and analyzed using the updated Coronary Artery Disease–Reporting and Data System (CAD-RADS) [29]. The percent diameter stenosis in every segment is categorized as 0% (no stenosis), 1–24% (minimal stenosis), 25–49% (mild stenosis), 50–69% (moderate stenosis), 70–99% (severe stenosis), and 100% (total occlusion). Interobserver disagreements are resolved by consensus.

The result of CCTA, as well as other CIT, will be provided to the local physician and he or she will make subsequent clinical decisions for the subject, such as additional CIT and clinical interventions like cardiac rehabilitation, OMT and coronary revascularization (CR), based on recommendations from clinical guidelines [3, 4, 26–29] and his or her cumulative clinical assessment of the subject.

### Study endpoint

The primary outcome, main secondary outcomes and other outcomes are described below and all outcomes are included Table 3. The primary endpoint of the study which indicates effectiveness of the diagnostic strategy is CCTA without obstructive CAD, defined as the summary of nonobstructive CAD, no sign of CAD and nondiagnostic result detected by CCTA according to each strategy during initial management. Obstructive CAD is defined as present if a patient had at least one lesion with ≥ 50% diameter stenosis at CCTA.

**Table 3 Tab3:** Study endpoints

Outcome	Topic	Description
Primary	CCTA without obstructive CAD	Summary of nonobstructive CAD, no sign of CAD and nondiagnostic result on CCTA during initial management
Secondary		
Safety	MACE	Composite of death, nonfatal MI and hospitalization due to unstable angina
	Individual cardiovascular endpoint	All-cause death, nonfatal MI and hospitalization due to unstable angina, respectively
	Exposure to radiation	Cumulative estimated radiation exposure related to cardiovascular care during the whole study period
	Procedural complications	Major: renal failure, stroke, severe bleeding and anaphylaxis or other complications if they lead to a hospital stay of at least 24 h Minor: complications not leading to prolonged stay, such as slight decrease of renal function, anaphylaxis and bleeding
Effectiveness	No. of cardiovascular procedures	Noninvasive CIT: exercise ECG, CCTA, PET-CT, MRI, myocardial perfusion imaging and stress echocardiography Invasive procedures: ICA and CR (CABG and PCI)
	Diagnostic metrics of CCTA during initial management	
	Diagnostic yield	No. of obstructive CAD/No. of CCTA×100%
	Proportion of necessary CCTA	No. of necessary CCTA/No. of CCTA×100%
	Proportion of normal CCTA	No. of normal CCTA/No. of CCTA×100%
	Other outcomes	HRQOL: Seattle Angina Questionnaire and visual-analogue scale of the European Quality of Life–5 Dimensions Time length of initial management: from successful eligibility to the end of initial management

CIT: cardiac imaging testing; MI: myocardial infarction; ECG: electrocardiogram; CR: coronary revascularization; HRQOL: health-related quality of life; MACE: major adverse cardiovascular events; CCTA: coronary computed tomography angiography; PET-CT: positron emission tomography-CT; MRI: magnetic resonance imaging; ICA: invasive coronary angiography; CABG: coronary artery bypass grafting; PCI: percutaneous coronary intervention

The key secondary endpoint indicating the safety of diagnostic strategy is the time to first MACE using composite of the following clinical events: All-cause death is used rather than cardiovascular death to eliminate the need for possibly difficult adjudication of causes of death, especially given the relatively low mortality; Nonfatal myocardial infarction (MI), including spontaneous and procedure-related, is defined according to the Fourth Universal Definition of Myocardial Infarction [33]; Hospitalization due to unstable angina is defined as an event in which the final diagnosis is myocardial ischemia (at least one of the following must be present: dynamic ST depression, ischemia on stress testing or significant epicardial coronary artery stenosis) and either of the following criteria is present: ischemic discomfort or equivalent symptoms requiring hospitalization within 48 h of symptoms and lasting at least 10 min at rest, or occurring in an accelerated pattern within 48 h of hospitalization. Only symptomatic events are defined as MACE. Asymptomatic events, such as silent MI is defined as incidental findings–if they will be detected at all.

In addition to the individual components of MACE, other secondary endpoints indicating the safety of diagnostic strategy include the followings: All-cause death, nonfatal MI, hospitalization due to unstable angina, overall exposure to radiation and complications (classified as major and minor) related to cardiovascular procedures which occur within 72 h. The estimated cumulative radiation exposure over the entire trial will be measured in milliSieverts using administered dose on CCTA, converted contrast agent dose for nuclear and administered radiation dose (kerma air product or dose length product) or fluoroscopy time for angiography [34].

Another secondary endpoint indicating the effectiveness of diagnostic strategy is resource use patterns (cumulative number of cardiovascular procedures during both initial management and follow-up, such as noninvasive and invasive CIT or CR). The diagnostic metrics of CCTA during initial management, including diagnostic yield proportion of normal CCTA and necessary CCTA, will be also calculated. Necessary CCTA is defined as obstructive CAD or alteration of OMT due to nonobstructive CAD on CCTA. Other effectiveness outcomes include time length of initial management and health-related quality of life (HRQOL).

### Study period and follow-up

The planned duration of the study is 24 months: 12 months for the enrollment period, defined as first visit of first subject to first visit of last subject and 12 months for the follow-up period. Study will preliminarily end when the following have occurred: at least 800 subjects have been randomized and 12 ± 1 month have elapsed since the last subject is randomized. All subjects will be followed for a minimum of 1 year and we will also try to continue the further follow-up after 1 year at 12-month intervals until death or withdrawal. Follow-up will be performed at 1st month (± 7 days), 3rd moth (± 14 days), 6th month (± 14 days), and 12th month (± 28 days) after randomization. The information of clinical visits is shown in Table 4. For outcome evaluation and recording of test complications, subjects have either a telephone call or clinic visit and the medical records are collected by trained interviewers. Data collected for suspected events are provided to the independent clinical event adjudication committee masked to the strategy assignment and intervention.

**Table 4 Tab4:** Time schedule

Timepoint	Initial	Follow up			
	visit	1st month (± 7 days)	3rd month (± 14 days)	6th month (± 28 days)	12th month (± 28 days)
Eligibility screen	×				
Informed consent	×				
Baseline data					
Demographics	×				×
General medical history	×				
Physical examination	×	×	×	×	×
ECG	×		×		×
Echocardiography	×				×
Laboratory testing	×		×		×
Randomization	×				
CCTA (if assigned)	×				
Clinical procedure data					
Other CIT	×	×	×	×	×
CR	×	×	×	×	×
Complications	×	×	×	×	×
OMT	×		×		×
Radiation	×	×	×	×	×
HRQOL	×			×	×
Cardiovascular endpoints	×	×	×	×	×
Length of stay	×				

CIT: cardiac imaging testing; ECG: electrocardiogram; CR: coronary revascularization; OMT: optimal medication treatment; HRQOL: health-related quality of life

### Sample size

The sample size calculation is performed using R (version 3.6.4; R Foundation for Statistical Computing, Vienna, Austria). To compute a weighted average rate as the projected rate of CCTA without obstructive CAD for a diagnostic strategy, data from previous literatures used in the sample size calculation include rate of CCTA without obstructive CAD in high risk group and distribution of subjects in low and high risk group.

For NICE strategy, theses parameters fluctuated over a wide range in different cohorts [12, 13, 16]. Thus, the distribution of subjects and the rate of CCTA without obstructive CAD in high risk group is estimated to be approximately 2:3 for low/high risk group and 62%, respectively, resulting in a projected rate of 3/(2 + 3)×57%=37.2%. Similarly, we assume that the projected rate of primary endpoint is 2/(2 + 3)×57%=22.8% for ESC strategy, based on the results of the original study [11] as well as our previous studies including one which investigated the RF-CL model in subjects with borderline PTP [16, 17].

For the analysis of primary endpoint, on 2-sided test 5% significance level and for the 1:1 allocation ratio, a sample size of 800 (allowing for 10% noncompletion) will provide more than 99% power between NICE and ESC arm. Thus, the final sample size is chosen to be 800 subjects (400 in each randomization group).

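### The NICE planning equation is false as printed (3/5 × 57% is 34.2%, not 37.2%), and the claimed power of more than 99% is just missed, at 98.9%, after the stated 10% noncompletion

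*Protocol article*

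**What the plan says.** All planning figures for the primary endpoint stand in the Sample size section of the protocol article. Each arm's projected rate of CCTA without obstructive CAD is the share of subjects classed as high risk multiplied by the rate of CCTA without obstructive CAD among them.

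- **NICE, inputs in prose:** the risk split and the high-risk rate are given as "approximately 2:3 for low/high risk group and 62%, respectively".
- **NICE, equation in the same sentence:** "resulting in a projected rate of 3/(2 + 3)×57%=37.2" per cent.
- **ESC:** "the projected rate of primary endpoint is 2/(2 + 3)×57%=22.8% for ESC strategy".
- **Test:** "on 2-sided test 5% significance level and for the 1:1 allocation ratio".
- **Power:** "a sample size of 800 (allowing for 10% noncompletion) will provide more than 99% power between NICE and ESC arm".
- **Total:** "the final sample size is chosen to be 800 subjects (400 in each randomization group").

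**The concern.** One sentence gives two different high-risk rates for NICE, 62% in words and 57% in the equation, and the equation does not yield the result printed after it. Nothing else in the article gives these rates, so a reader cannot settle the matter from another section. The section also says that the NICE parameters varied widely between cohorts, so outside plausibility does not settle it either.

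The factor determines the planned effect. With 62% the planned difference is 37.2 − 22.8 = 14.4 percentage points. With 57% it would be 34.2 − 22.8 = 11.4 points.

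The power sentence raises a second, smaller question. It says that the 800 already allow for 10% noncompletion, so the stated power should hold with 720 evaluable subjects. The allowance bears on the primary analysis, because the modified intention-to-treat set in the Statistical plan leaves out subjects who withdraw before the assigned intervention.

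**Working it through.** **Inputs, all from the Sample size section.** Two-sided 5% level; 1:1 allocation, 400 per arm; 10% noncompletion, so 800 × 0.9 = 720 evaluable, or 360 per arm; NICE low:high split 2:3; NICE high-risk rate printed as both 62% and 57%; ESC high-risk share 2/5 with a rate of 57%. The Statistical plan compares proportions by chi-square or Fisher's exact test.

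**Step 1: planning rates.**

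- ESC: 2/5 × 57% = 22.8%. This matches the text.
- NICE with the factor in the equation: 3/5 × 57% = 34.2%. This does not match the printed 37.2%.
- NICE with the rate in the prose: 3/5 × 62% = 37.2%. This matches.

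Of the three printed NICE quantities (62%, 57%, 37.2%), only the 57% is out of line.

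**Step 2: the plan's own power figure.** Two-proportion normal approximation with pooled variance under the null:

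power = Φ{ [ |p1 − p2| − 1.96 × √(2p̄(1 − p̄)/n) ] / √( [p1(1 − p1) + p2(1 − p2)]/n ) }, where p̄ = (p1 + p2)/2.

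For p1 = 0.372 and p2 = 0.228: p̄ = 0.300, 2p̄(1 − p̄) = 0.4200, and p1(1 − p1) + p2(1 − p2) = 0.4096.

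- n = 400 per arm: (0.144 − 1.96 × 0.03240)/0.03200 = 2.515, so power is **99.4%**. The stated figure is reproduced with all 800 evaluable.
- n = 360 per arm: (0.144 − 1.96 × 0.03416)/0.03373 = 2.284, so power is **98.9%**.

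Other formulas at 360 per arm give 98.95% (unpooled variance), 98.9% (arcsine) and 98.6% (continuity-corrected). None exceeds 99%.

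**Step 3: where 99% is reached.** The pooled formula needs 368 evaluable per arm, or 736 in total. That is 736/800 = 92%, so the claim holds up to 8% loss and is just missed at 10%, by 8 subjects per arm.

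**Step 4: the conditional case, if 57% were the intended factor.** For p1 = 0.342 and p2 = 0.228: p̄ = 0.285, 2p̄(1 − p̄) = 0.4076, and p1(1 − p1) + p2(1 − p2) = 0.4011.

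- n = 400 per arm: (0.114 − 1.96 × 0.03192)/0.03166 = 1.624, so power is 94.8%.
- n = 360 per arm: (0.114 − 1.96 × 0.03365)/0.03338 = 1.440, so power is 92.5% (91.3% to 92.7% across the other formulas).

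| NICE rate vs ESC rate | 400 per arm | 360 per arm | Evaluable per arm for 99% |
|---|---|---|---|
| 37.2% vs 22.8% (62%) | 99.4% | 98.9% | 368 |
| 34.2% vs 22.8% (57%) | 94.8% | 92.5% | 572 |

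**The case against.** The best defence is that the document nearly resolves the conflict itself. The 62% and the 37.2% fit together, 57% is the ESC multiplier one sentence later, and the stated power comes out with 37.2% but not with 34.2%. On that view this is a misprint, and a figure of 98.9% against a claim of more than 99% is rounding. Most of this stands. It is why the 62% reading should be treated as the likely one and why the point is minor. It does not make the printed equation true, and only the sponsor can confirm which number was used.

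A reader might infer more than the text supports, in three ways.

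- **That power is equally likely to be 92.5%.** That figure needs a NICE rate of 34.2%, which the article never states and which contradicts both the 62% and the 37.2%. It is a conditional result only.
- **That more than 99% requires all 800 subjects to be evaluable.** It does not: 736 are enough under the 37.2% rate.
- **That power falls well below these figures once physicians depart from the recommendation.** The projected rates do assume that referred subjects are scanned and deferred subjects are not. The article gives no departure rates, so any such power figure would rest on invented inputs. The text also limits the exposure: the endpoint covers CCTA during initial management, deferred subjects have no immediate imaging, and people with a clear preference for or against imaging are excluded.

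**Conclusion.** The point holds as a minor correction. The NICE equation is arithmetically wrong as printed and conflicts with the rate in its own sentence. The 57% is the likely misprint, but the article alone cannot establish that.

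Under the reading that the document supports, the power claim is true for 400 per arm (99.4%) and short by about 0.1 percentage point for the 360 per arm that its own allowance implies (98.9%). These figures assume the printed ESC rate of 22.8%, equal loss in the two arms and a standard two-proportion test at the two-sided 5% level. Even if 57% was intended, power stays above 90%, so the documents do not support calling the trial underpowered. No endpoint, test or sample size is affected.

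**What to change.** In the Sample size section:

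1. Confirm the intended high-risk rate for NICE against the original calculation.
2. If it is 62%, print the equation as 3/5 × 62% = 37.2% and give power as about 98.9% with 720 evaluable subjects (99.4% with all 800).
3. Only if it is 57%, print the NICE rate as 34.2% and give power as about 92.5% with 720 evaluable subjects.

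The cost is a change of wording and a slightly less favourable power statement. The total of 800 stays as it is, and nothing in the conduct of the trial changes.

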### Statistical plan

All statistical analyses are performed by the statistical and data coordinating group using R (version 3.6.4; R Foundation for Statistical Computing, Vienna, Austria) or MedCalc (version 15.2.2; MedCalc Software, Mariakerke, Belgium). Two-tailed P < 0.05 is considered statistically significant. The primary analysis is conducted according to a modified intention-to-treat (ITT) principle. All subjects who undergone randomization and don’t withdraw before assigned intervention (CCTA or no further testing) or other CIT during the initial management will be included. Categorical variables will be described by counts and proportions and compared by chi-square tests or fisher exact test. Continuous variables will be described by mean and standard deviation or median and interquartile range and compared through t test or Mann-Whitney U tests.

The comparison of primary outcome between two diagnostic strategy regimens was expressed as risk ratio, along with 95% confidence interval and number needed to treat. The per-protocol analysis excluding subjects with insufficient compliance or with other major protocol deviation(s) and the traditional ITT analysis including all subjects who are randomized will be performed as prespecified sensitivity analyses. Different diagnostic metrics, such as initial CIT without positive result, unnecessary CCTA and CCTA with no sign of CAD, will also be considered as sensitivity analyses. To explore the consistency of strategy effectiveness according to specific subject characteristics, a limited number of prespecified subgroup analyses for the primary endpoint are conducted using interaction terms in log-binomial regression models. We will also undertake a hierarchical analysis (giving priority to clinical importance of the components of the composite outcome rather than time to first event: Death > nonfatal MI > hospitalization due to unstable angina > CCTA without obstructive CAD > referral to CIT) using the matched win ratio method [35].

Kaplan-Meier curves for cumulative event-free estimates survival from the first of the following: endpoints of concern, death, the end of 1-year follow-up period or loss to follow-up, are presented graphically and the Log-rank test will be used to calculate the corresponding p. A Cox proportional hazards model will be used to compare the time to study endpoint and to account for heterogeneity among subjects, the models will be adjusted for pre-specified and minimization covariates, which are selected on the basis of their established importance in other CCS cohorts, highly complete data capture, and a sufficient range of values for risk to vary among subjects meeting study eligibility criteria.

Multiple imputation using the R package Multivariate Imputation by Chained Equations algorithm will be used for missing data in ITT analysis of primary endpoint to ensure all subjects could be included in the ITT analysis, as well as HRQOL analysis [36]. Strategy comparisons of HRQOL are performed by using a mixed-effects regression model to account for repeated measures within a subject, with strategy, time point, baseline HRQOL and minimization covariates as predictor variables. If the analyses above show significant differences in study endpoints, information from the study and other sources, including medical costs, resource use, HRQOL and clinical outcomes will be used for the potential cost-effectiveness analyses to quantify the incremental cost per quality-adjusted life year gained.

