### Randomization and blinding

After collection of baseline clinical data, eligible subjects will be randomized (in blocks of 2) sequentially 1:1 to start double-blind diagnostic strategy with 1 of 2 regimens: NICE and ESC. The computerized randomization list is generated independently by a statistician from the statistical and data coordinating group who will not participate rest of the study. Both investigators and subjects are blinded to the allocation process until the end of trial (sequentially numbered, opaque, sealed envelope will be used to conceal allocation). Once the subject is ready for randomization, the corresponding envelope will be opened by the independent strategy assignment expert panel consisting of cardiologists who will not participate rest of the study. The expert panel determine whether the subject should be referred to CCTA according to the given diagnostic strategy (see below) and only send the final recommendation about referral or deferral of CCTA to the physician and subject.

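### Both risk classes can be computed from baseline data, but the plan's whole-arm comparisons ignore them; using them would sharpen the primary estimate and undilute the safety comparison at no cost

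*Protocol article*

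**What the plan says.** **Classification.** Table 2 (Diagnostic strategies) defines the NICE low-risk group as "Both normal ECG and nonanginal chest pain"; everyone else is high risk. The ESC class follows from the ESC pretest probability (age, sex, type of pain) and, in the borderline band, from the RF-CL score, which adds five risk factors. Every input is a baseline item.

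**Order and masking.** Under Randomization and blinding, baseline data come first, then randomisation in blocks of 2 with no stratification factor named. The expert panel applies the allocated strategy and will "only send the final recommendation about referral or deferral of CCTA to the physician and subject".

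**Analysis.** Under Statistical plan, categorical variables are "compared by chi-square tests or fisher exact test", and for the primary endpoint: "The comparison of primary outcome between two diagnostic strategy regimens was expressed as risk ratio, along with 95% confidence interval and number needed to treat". Time-to-event outcomes get a log-rank test and a covariate-adjusted Cox model; HRQOL gets an adjusted mixed model. The stated sensitivity analyses are per-protocol, full ITT, other diagnostic metrics and a win ratio. None uses agreement between the two rules. Subgroup factors and covariates are mentioned but not listed.

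**Safety aim.** Overall design and objectives sets the key secondary objective as assessing whether the strategies show no significant difference in MACE.

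**The concern.** The trial randomises which rule is applied, but a subject receives only the rule's output. If both rules refer, or both defer, the advice is the same whichever envelope is opened, and it tells nobody which arm the subject is in. The expected arm effect in such subjects is zero for every outcome, provided the masking holds.

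Two things follow. For the primary endpoint, the joint class predicts the outcome strongly, because a deferred subject can hardly have a negative CCTA during initial management. Leaving it out wastes precision. For MACE, the whole-arm difference equals the discordant share times the difference among discordant subjects. When the stated hope is to find no difference, this shrinkage favours the hoped-for answer. Table 2 also permits disagreement in both directions (referred by NICE only, or by ESC only), so opposing effects could partly cancel in the whole-arm figure.

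**Working it through.** **1. The plan's own figure.** Sample size claims "more than 99% power between NICE and ESC arm" for 800 subjects in all (two-sided 5% level, equal allocation, 10% loss), at 37.2% (NICE) against 22.8% (ESC). The pooled rate is 30%. Power = Φ[(0.144 − 1.96·√(2·0.30·0.70/n)) / √((0.372·0.628 + 0.228·0.772)/n)].
- n = 400 per arm: 99.4%.
- n = 360 per arm (after 10% loss): 98.9%.

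The stated power reproduces. The NICE inputs are "estimated to be approximately 2:3 for low/high risk group and 62%, respectively", but the formula line reads "resulting in a projected rate of 3/(2 + 3)×57%=37.2". 0.6 × 62% gives 37.2% and 0.6 × 57% gives 34.2%. That slip is a separate matter; I use 37.2% and check 34.2% in step 3.

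**2. Discordant share.** The planning splits are 60% high risk under NICE and 40% under ESC. The joint split is not given. The margins bound discordance between 20% (ESC-high nested in NICE-high) and 100% (disjoint); independence would give 0.6·0.6 + 0.4·0.4 = 52%.

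**3. Primary endpoint, nested case, 360 per arm.** Assumptions: every referred subject and no deferred subject has CCTA in initial management, and the rate is 57% in ESC-high subjects.
- Both refer: 40% of subjects, 57% in both arms.
- NICE only: 20%, (0.372 − 0.228)/0.20 = 72% in the NICE arm, 0% in the ESC arm.
- Both defer: 40%, 0% in both arms.

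Unstratified SE = √[(0.372·0.628 + 0.228·0.772)/360] = √(0.4096/360) = 0.0337.

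Stratified SE = √[(0.40·2·0.57·0.43 + 0.20·0.72·0.28)/360] = √(0.2364/360) = 0.0256.

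The variance ratio is 0.4096/0.2364 = 1.73. Under the same assumptions with more discordance the stratified SE stays at 0.0257–0.0258. Power rises from 98.9% to about 99.99%.

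With 34.2% for NICE, the NICE-only rate is 57%. The SEs are √(0.4011/360) = 0.0334 and √(0.2451/360) = 0.0261, so the gain is similar.

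**4. MACE.** The protocol gives no 1-year MACE rate for the trial population. I assume rate r in all classes and discordant share d, with 360 per arm.
- Whole-arm half-width: 1.96·√(2r(1−r)/360).
- Discordant subjects only, multiplied back by d to the whole-population scale: the same figure times √d. This takes the concordant effect as zero.

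| r | whole arm | d = 20% | d = 30% | d = 40% |
|---|---|---|---|---|
| 1% | 1.45 | 0.65 | 0.80 | 0.92 |
| 2% | 2.05 | 0.91 | 1.12 | 1.29 |
| 3% | 2.49 | 1.11 | 1.36 | 1.58 |

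(percentage points)

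Within discordant subjects, unscaled, at r = 2%: 1.96·√(0.0392/72) = ±4.6 points at d = 20%, and 1.96·√(0.0392/108) = ±3.7 at d = 30%. With 400 per arm (80 and 120 discordant) these are ±4.3 and ±3.5. Expected events per arm are 72·0.02 = 1.4 and 108·0.02 = 2.2, so the normal approximation is only indicative.

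**5. Power if MACE doubles from 2% to 4% in discordant subjects.** At d = 30% the whole-arm rates are 2.6% against 2.0%. Power is 7.7% whole-arm and 13.6% in discordant subjects. At d = 50% it is 13.5% and 19.8%.

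**The case against.** The primary objective is to compare the rates that the two strategies produce, in a pragmatic trial. The all-subject contrast is that estimand, and the planned risk ratio estimates it without bias at about 99% power. Stratification factors and covariate lists are commonly left to an analysis plan that is not shown. **All of this stands.** A reader might infer that the primary comparison is invalid or underpowered; the documents do not support that. The gain is in precision, and under the planning assumptions it would not change the conclusion.

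A reader might also infer that the plan makes no adjustment. It does: the Cox and HRQOL models carry covariates. That answers part of the point only. However adjusted, the strategy coefficient still averages over concordant subjects, so the dilution remains.

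Nor do the documents show that both classes are already known for each subject. The panel is described as applying only the allocated rule. The classes are computable, not documented as computed. And concordant subjects do not all add noise to the primary endpoint: those deferred by both rules contribute zeros in either arm.

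Finally, the MACE gain looks large only on the whole-population scale, and the Discussion already concedes that low event rates limit inference on MACE. Its registry figures for subjects classed as low risk (1.1% and 0.7% over 17 months) suggest events could be rarer still. This also stands, and is why the discordant-subject analysis can only be supplementary.

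**Conclusion.** The point holds as a free improvement. The planned analyses, as described, make no use of a baseline classification that determines where any arm effect can occur. For the primary endpoint, stratifying by joint class lowers the SE from 3.4 to 2.6 points in the nested case. For MACE, the benefit is a comparison not pulled towards no difference by subjects who could not differ. At 2% MACE the half-width on the whole-population scale goes from about 2.0 points to about 0.9–1.3 for 20–40% discordance.

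It would be wrong to infer that this rescues the safety question. Among discordant subjects the interval remains about ±3.5 to ±4.6 points with one or two events per arm, and power against a doubling stays below 20% in the cases worked.

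The figures rest on an assumed discordant share, assumed MACE rates equal across classes, CCTA following the recommendation, and masking that keeps the concordant effect at zero.

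**What to change.** 1. Have the statistical and data coordinating group compute both classes for every subject from pre-randomisation data and lock them before outcomes are seen. Withhold them from sites, since a known class together with the recommendation would reveal the arm of a discordant subject.
2. Keep the all-subject estimand. Report the primary risk difference and risk ratio standardised over the four joint classes (both refer, both defer, NICE only, ESC only): average the class-specific risks in each arm over the common class distribution, then form the difference and ratio. Choose a variance method that tolerates strata with no events. Stratum-specific ratios or a saturated log-binomial model would fail there.
3. Prespecify supplementary comparisons of MACE, radiation, procedures and HRQOL in discordant subjects beside the all-subject results, by direction of discordance where numbers allow. Use exact methods for MACE and give the interval on the discordant scale as well as the whole-population scale.
4. State that the discordant share and MACE rate are assumptions, and that MACE remains underpowered in either analysis.

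The cost is a calculation on variables already collected and a paragraph in the analysis plan. No extra subjects, visits or data are needed.
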